### Study procedures

**
*Inclusion criteria*
**

•   A history of fever at presentation for ≥ 72 hours and a documented fever (≥37.5°C (axillary) or ≥38°C (oral))

•   Age ≥ 2 years (and ≥ 10kg) to 65 years

•   No clear focus of infection on initial clinical evaluation

•   Malaria rapid diagnostic test (RDT) negative; dengue non-structural protein NS1 RDT negative; scrub typhus RDT negative; C-reactive protein (CRP) rapid test ≥10 mg/L

•   Able to take oral treatment

•   Able to attend for follow-up and can be contacted by telephone

•   Written fully informed consent to participate in the study including assent for children in addition to parental/legal guardian consent.

**
*Exclusion criteria*
**

The participant may not enter the trial if ANY of the following apply:

•   History of fever for >14 days

•   Pregnant or positive pregnancy test or breast-feeding

•   Presence of clinical symptoms or signs indicating a focal infection such as pneumonia; urinary infection, meningitis, eschar

•   Obtundation, haemodynamic shock, visible jaundice, gastrointestinal bleeding or any signs of severe disease that may require immediate hospitalisation

•   Being treated for tuberculosis (TB) or human immunodeficiency virus (HIV) or severe acute malnutrition

•   Patients with cardiac disease

•   Patient requiring intravenous antibiotics for any reason

•   Previous history of hypersensitivity to any of the treatment options

•   Either of the trial drugs are contraindicated for any reason (e.g. drug interactions)

•   Has received azithromycin or cefixime in the last five days

•   Receiving another antimicrobial and responding clinically to the treatment as judged by the attending clinician.

•   Being on another drug (for example certain kinds of anti-depressants, or anti-convulsants) that may also cause prolonged QT interval

•   Positive polymerase chain reaction (PCR) test for coronavirus disease 2019 (COVID-19) before or after randomisation

**
*Screening and eligibility.*
** The non-specific clinical presentation of typhoid fever can make it difficult to distinguish typhoid from other causes of an acute undifferentiated febrile illness such as malaria and dengue based on clinical history, physical examination and initial laboratory investigations alone
^
28,
30
^. There are no satisfactory rapid diagnostic tests for typhoid fever
^
31

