### Laboratory testing and sample handling

Initial trial visit

Ethylenediaminetetraacetic acid (EDTA) tube blood (1-1.5mL) for haematology (white cell count and differential, haemaglobin/haematocrit, platelet count) (
Table 2)Heparinised blood (2mL) for sodium, potassium, urea, creatinine, semi quantitative C reactive protein (CRP) test, bilirubin, aspartate transaminase (AST) and alanine transaminase (ALT)EDTA blood (2mL) will be used for malaria RDT, dengue RDT, scrub typhus RDT, and CRP RDT. Remaining blood centrifuged and plasma and blood pellet stored at -20°C /-80°C for future diagnostic, biomarker, pharmacokinetic studies and genetic analysis. Centrifugation and blood storage will be done ONLY if the patient fulfils the inclusion criteria.Blood culture (3-8mL depending on age). Urine sample will be collected from all participants and stored at -20°C/-80°C for later and tested by bioassay for antimicrobial activity.Faecal sample will be collected from all participants for standard bacterial culture (to detect
*S*. Typhi or Paratyphi). DNA (deoxyribonucleic acid) will be extracted from the stool and stored for later diagnostic microbiome studiesNasopharyngeal swab test to detect COVID-19 using a PCR test or as per current existing rules and regulations of the hospital. Sample collection will be carried out following all the guidelines of the local hospital for handling potential COVID-19 patients.Rapid diagnostic tests: - For the malaria and dengue NS1 antigen RDTs locally available tests will be used. The scrub typhus RDT will be Scrub Typhus Detect™ IgM Rapid Test (InBios, Seattle, USA). For CRP screening we will use a semi-quantitative lateral flow test (ACTIM CRP tests, Medix Biochemica) that uses a drop of blood and gives a result in 5 minutes. It has thresholds of 10, 40 and 80mg/L so will give the right cutoff for inclusion, and some information on how high CRP is when it is ≥10mg/L.

Follow up trial visits

A blood culture will be repeated at the day 7 follow up visit and at any time during follow-up if there is a clinical deterioration in the participant or a clinical suspicion of relapse after review and assessment by the trial physician. Stool cultures for
*S*. Typhi or
*S.* Paratyphi on day 0, 7, 14, 28. Also on day 90 if the day 0 blood/stool culture positive for salmonella.

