### Sample size calculation

We will randomize 1500 subjects (750 per arm) within 2 years, with between 125 and 250 recruited per year at each site. Assuming a treatment failure risk of 15% in the group given azithromycin alone, the sample size will guarantee 92% power to detect an absolute risk reduction of 6% (from 15% to 9%) and 80% power to detect an absolute risk reduction of 5% (from 15% to 10%) in the group given the combined antimicrobials at the two-sided significance level of 5% allowing for up to 10% loss to follow up. In case of a lower treatment failure risk of 10% in the control arm, the trial will have 94% power to detect a 5% absolute risk reduction (from 10% to 5%) and 77% to detect a 4% reduction (from 10% to 6%).

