### Statistical and analytical plans

The statistical aspects of the study are summarised here with details fully described in a statistical analysis plan (SAP) which will be finalised before any analysis takes place. The primary endpoint of this trial is the composite outcome of treatment failure by the 28th day after the initiation of treatment. Subjects who withdraw from the study prior to day 28 without treatment failure will be treated as right-censored. The primary comparison of the absolute risk of treatment failure until day 28 between the treatment arms will be based on Kaplan-Meier estimates and corresponding standard errors according to Greenwood’s formula.

The time to treatment failure from the onset of treatment will be described using Kaplan-Meier curves and compared between the treatment arms with a Cox proportional hazards model with treatment assignment as the primary covariate and adjustment for blood culture result (positive for
*S.* Typhi or
*S.* Paratyphi vs. negative), age (children (<16 years) and adults (≥16 years)), and country. Time to treatment failure from symptom onset will be analysed in the same way but subjects will be considered as left-truncated at the time of onset of treatment to account for the fact that they were not under observation before that timepoint.

Fever clearance time will be calculated using temperatures recorded twice per day and treated as an interval-censored outcome. The fever clearance time distribution will be estimated using the non-parametric maximum likelihood estimator (NPMLE) and comparisons between the arms will be based on a parametric Weibull accelerated failure time model. 

A two-sided significance level of 5% will be applied to all efficacy analyses. The primary analysis population for all analyses is the modified intention to treat (ITT) population consisting of all patients who have been randomised to the trial and received at least one dose of study treatment. Analysis will be according to the randomized treatment arm. Subjects, who were mistakenly randomised or withdrew before the first dose of study treatment was given, will be excluded. Subjects who were unblinded will be included in the ITT population.

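### The stated secondary models make no use of days of fever, day-0 temperature or CRP band, all obtained at entry: a missed efficiency gain, not an error

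*Protocol article*

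**What the plan says.** The section Statistical and analytical plans of the protocol article describes two secondary time-to-event models.

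- **Time to treatment failure from first dose:** a Cox model "with treatment assignment as the primary covariate and adjustment for blood culture result", age group (under 16 years or older) and country. That is the whole list.
- **Fever clearance time:** treated as interval-censored from twice-daily readings, with "comparisons between the arms will be based on a parametric Weibull accelerated failure time model". No covariate is named and none is ruled out.

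A second Cox analysis runs from symptom onset, with participants left-truncated at the start of treatment. The same section calls itself a summary and refers to an SAP for full detail.

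Three baseline measures are available for everyone:

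- **Days of fever.** Entry requires "A history of fever at presentation for ≥ 72 hours and a documented fever", and "History of fever for >14 days" is an exclusion, so the range is 3 to 14 days.
- **Day-0 temperature.** It is an entry criterion and is scheduled in Table 2. It is taken by the axillary or the oral route, with different fever thresholds.
- **CRP band.** The screening test has thresholds at 10, 40 and 80 mg/L and is said to give "some information on how high CRP is when it is ≥10mg/L".

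**The concern.** Fever clearance time is defined as the time until temperature stays below a fixed threshold for 48 hours. How high the temperature starts, and how long the illness has already run, are therefore plausible predictors of it. Fever at 168 hours is also a component of treatment failure, so the same measures may predict the Cox outcome. Fever clearance is the first secondary endpoint, and the article's rationale cites shorter clearance times as clinical evidence for adding a second drug. If the entry measures are prognostic and stay out of the models, the fever-clearance interval is wider than it needs to be and both models give up some power, although the data are already being collected.

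**Working it through.** **The plan's own power figures.** Inputs from Sample size calculation: "We will randomize 1500 subjects (750 per arm) within 2 years", "allowing for up to 10% loss to follow up", two-sided 5%. This leaves 750 × 0.9 = 675 per arm. With a pooled-variance test of two proportions:

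- 15% v 10%: null SE = √(2 × 0.125 × 0.875 / 675) = 0.01800; alternative SE = √((0.1275 + 0.0900) / 675) = 0.01795; z = (0.05 − 1.96 × 0.01800) / 0.01795 = 0.82; power 79.4% (stated 80%).
- 15% v 9%: 92.5% (stated 92%). 10% v 5%: 93.8% (94%). 10% v 6%: 77.4% (77%).

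These figures reproduce. They concern the unadjusted risk comparison, so the covariates of the secondary models do not enter them.

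**Fever-clearance model.** The article gives no prognostic strength, no spread of clearance times and no target effect, so all three are assumptions. R² is the share of log fever-clearance variance explained by the entry measures. Each simulation below uses 1350 patients, 12-hourly readings and an interval-censored Weibull model, fitted with and without a baseline score. The result is the variance of the log time ratio with adjustment divided by that without.

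| Setting | R² | Variance ratio |
|---|---|---|
| Time ratio 0.93 | 0, 5%, 10%, 20% | 1.01, 0.89, 0.74, 0.64 |
| Time ratio 0.93, Weibull scale 0.45, 1000 runs | 5%, 10%, 20% | 0.86, 0.75, 0.61 |
| Log time ratio −0.08, Weibull scale 0.5, 900 runs | about 2%, 9%, 18% | 0.94, 0.84, 0.66 |
| Time ratio 0.93, control scale parameter 5.2 days, 300 runs | 5%, 10%, 20% | 0.88, 0.79, 0.63 |

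The last row comes from empirical SEs, for example (0.0249 / 0.0266)² = 0.88.

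To translate into power for an analysis that has 80% without adjustment, with variance ratio v: power = Φ((1.96 + 0.842) / √v − 1.96).

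- v = 0.89: 2.802 / 0.943 − 1.96 = 1.01, power 84%.
- v = 0.74: 2.802 / 0.860 − 1.96 = 1.30, power 90%.
- v = 0.64: 2.802 / 0.800 − 1.96 = 1.54, power 94%.

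The simple rule v = 1 − R² gives smaller gains: 82%, 84% and 88% at R² of 5%, 10% and 20%. The simulated gain is larger, and the excess depends on the assumed data-generating model.

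On bias, in the 900-run setting the unadjusted mean estimates were −0.0800, −0.0796 and −0.0773 against a true value of −0.08.

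**Cox model.** Inputs: 675 per arm, 15% v 10%. Expected events = 675 × (0.15 + 0.10) = 168.75. The SE of the log hazard ratio is about 2 / √168.75 = 0.154. It is set by the number of events, which adjustment does not change. Simulation with 1500 runs per setting:

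| Log hazard ratio of covariate, per SD | SE, unadjusted and adjusted | Mean log hazard ratio for treatment, unadjusted → adjusted | Power |
|---|---|---|---|
| 0 | 0.158, 0.158 | −0.430 → −0.431 | 79.2% → 78.9% |
| 0.3 | 0.158, 0.158 | −0.440 → −0.443 | 80.8% → 81.5% |
| 0.5 | 0.158, 0.158 | −0.442 → −0.451 | 80.8% → 82.5% |
| 0.8 | 0.158, 0.158 | −0.438 → −0.464 | 79.3% → 83.7% |

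The gain is 0.7, 1.7 and 4.4 points, and it comes from a larger conditional hazard ratio.

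**The case against.** The strongest reply is that a condensed article naming a model without covariates has not decided against them. It defers detail to an SAP that is not shown, and the covariates of a secondary model are commonly left there. This stands. A reader might infer that the fever-clearance comparison is unadjusted by design; the text does not say so. It is fair to note only that the same section does list covariates for the Cox model, and that this list omits the entry measures.

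Second, the prognostic strength is assumed. Entry rules narrow all three measures: 3 to 14 days of fever, temperature above a threshold, CRP of at least 10 mg/L and known only in bands. Their R² may therefore be low. This also stands, and it is why the result is a range that starts at no gain.

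Third, a time ratio of 0.93 is a small effect: 0.07 × 5.2 days × 24 = 8.7 hours, less than one reading interval. For a ratio of 0.90, the unadjusted SEs of 0.0266 (R² 5%) and 0.0301 (R² 30%) already give Φ(0.1054 / 0.0266 − 1.96) = 98% and Φ(0.1054 / 0.0301 − 1.96) = 94%. So the power gain matters only for small effects. The narrower interval is gained whatever the effect.

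Fourth, illness duration already enters the Cox analysis from symptom onset through its time scale. That is correct, but it does not adjust the analyses from first dose. The planned subgroup analyses of fever clearance by culture result, age, country and site are not adjustment either.

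A reader might go further and infer a validity problem. One simulation under no effect did show the unadjusted Weibull test rejecting in 5.3% to 7.7% of runs at R² of 20% to 30%, against 3.3% at R² of 0. It needs predictors stronger than anything the article supports and it reflects model-based standard errors under a misspecified Weibull shape. It is not grounds for calling the plan wrong.

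**Conclusion.** The point holds as a minor, nearly free improvement to two secondary models. The stated Cox list leaves out three measures obtained at entry, and the article names no covariates for the fever-clearance model. With an assumed R² of 5% to 20%, the variance of the log time ratio would fall by roughly 10% to 35%; with R² of 0 it would not change. For the Cox model a reader might infer lost precision, but the SE stays at 0.158. The gain there is about 1 to 4 points of power under the assumed covariate strengths, and the unadjusted hazard ratio is a different, less conditional quantity rather than a mistaken one. Nothing here makes the trial underpowered: the primary comparison and its four power figures are unaffected.

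**What to change.** In the SAP, before unblinding:

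1. For the fever-clearance model, name the covariates: culture result, age group and country or site, plus days of fever at first dose, day-0 temperature with its measurement route, and CRP band (10–39, 40–79, 80 mg/L or more).
2. Add the same three entry measures to the Cox model from first dose, and state that its hazard ratio is then conditional on them.
3. Report the estimates without the added terms alongside.

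No new data are needed. The entry measures use five degrees of freedom (days 1, temperature 1, route 1, CRP band 2). With the six already in the Cox model (treatment 1, culture 1, age 1, country 3) that makes 11, or 168.75 / 11 ≈ 15 events per parameter at 15% v 10%. At 10% v 5% there would be 675 × 0.15 ≈ 101 events, about 9 per parameter. The culture-confirmed population will have fewer, so the SAP may keep a shorter list there. The other cost is the changed interpretation of the hazard ratio.

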### Data collection and management

Data collection is the responsibility of the clinical trial staff at the site under the supervision of the site PI. The investigator is responsible for ensuring the accuracy, completeness, legibility, and timeliness of the data reported. Clinical data (including adverse events (AEs), concomitant medications, and expected adverse reactions data) and clinical laboratory data will be entered into CliRes, a 21 CFR Part 11-compliant data capture system provided by the OUCRU IT department. The data system includes password protection and internal quality checks, such as automatic range checks, to identify data that appear inconsistent, incomplete, or inaccurate. Clinical data will be entered directly in tablets connected to the central database collection site at the Nepal CTU. The sites can access their data in the central data base which will be password protected.

The primary data is collected onto the CRF while interviewing the patients at the outpatient department in the hospital. There will be 1500 patients, with 5 hospital visits each, 2 home visits by CMA and data obtained from the telephone calls. On average, each patient will have a CRF, which contains around 23–25 pages with all patient details. The participants will be identified by a unique trial specific number and/or code in any database. The name and any other identifying detail will NOT be included in any trial data electronic file.

Only authorized users with specific delegation will be given access to the database. These users will be trained according to their delegation before working with the database. All the changes made in the database will be tracked and will be kept as a part of documentation. Data storage will be in the central database in the Nepal CTU and backed up in Vietnam. All the sites will be able to access their data secured with password from the central site. All the metadata will be specified during the database development which includes data type, coding, table and column names, validation etc. The data required for the analysis from the extracted database will be derived from the metadata dictionary.

### Data preservation strategy and standards

All the physical data from the CRFs will be collected in an electronic tablet in each site which will feed into the central electronic data base which will be stored securely at the OUCRU Nepal server with regular backup in Vietnam. The data security standards in place at each site are detailed in the unit’s system level security policy which adheres to the standard for information security management ISO27001. All the trials participants’ anonymity and confidentiality will be maintained throughout the study period. The same will be ensured with the data of the participants. They will be identified by the specific study numbers rather than their name or any other identifiable characters. All the users involved in the data management will be trained before allocation to the specific tasks related to patient details.

### Data sharing and access

Access to data for outside party will be given only after approval by the Trial steering group which will be through application to the group. OUCRU CTU SOP ensures participants’ anonymity and Confidentiality during the data sharing procedure. The Nepal CTU will ensure the trial is `discoverable’ through trial registration.

### Safety reporting

The definitions of the EU Directive 2001/20/EC Article 2 based on the principles of the International Conference on Harmonization good clinical practice (ICH GCP) apply to this trial protocol. Adverse effects will be classified and graded according to the Common Terminology Criteria for Adverse Events (CTCAE) system. All serious and grade 3 or 4 AEs will be compared between arms and reported by frequency per arm. An independent DMC will oversee the safety of the trial participants Definitions. The definitions of the principles of ICH GCP apply to this trial protocol. All grade 3 or 4, or serious AEs and ARs, whether expected or not, should be recorded in the CRF. Non-serious grade 1 or 2 AEs need not be recorded unless they are thought to be related to the IMP or they result in a change or interruption in treatment.

Procedure for immediate reporting of serious adverse events (SAEs)

Site study team will complete an SAE report form for all reportable SAEs.Where the SAE requires immediate reporting, the SAE report form will be scanned and emailed to trial coordinating team immediately i.e., within 24 hours of site study team becoming aware of the event. The team will acknowledge receipt of this report.Site study team will provide additional, missing or follow up information in a timely fashion.The assessment of expectedness will be conducted within 48 hours by the Site study team and the Coordinating Centre team within three days of reporting.All deaths will be reported to the trial coordinating team immediately i.e., within 24 hours of site study team becoming aware of the event and to the chairman of the Data Safety Monitoring Board (DSMB)

All SAEs other than those defined in the protocol as not requiring reporting must be reported on the SAE reporting form to CTU within 24 hours of the trial coordinating team becoming aware of the event. 

SAEs will be reported as soon as possible to the site ethics committee (EC). A written report will be sent as soon as possible but not later than 2 working days (for SAE resulting in death or life threatening). Additionally, the detailed report of the SAE should be submitted to the IRBs within 15 days. Additional medical information of the SAE’s development must be reported in other report until the trial subjects recover or stabilize without further change expected. Other AEs should be recorded, summarized and reported in the annual report form and the final report form. All SAEs will be reported to OxTREC in the annual review form and to the DMC in accordance to the DMC charter.

### Risk assessment

The trial will be conducted in accordance with the current approved protocol, GCP, relevant regulations and standard operating procedures including precautions regarding COVID-19. A risk assessment and monitoring plan will be prepared before the study starts and will be reviewed as necessary over the course of the trial to reflect significant changes to the protocol or outcomes of monitoring activities.

### Monitoring

Regular monitoring will be performed according to the trial specific monitoring plan. Data will be evaluated for compliance with the protocol and accuracy in relation to source documents as these are defined in the trial specific monitoring plan. Following written standard operating procedures, the monitors will verify that the clinical trial is conducted and data are generated, documented and reported in compliance with the protocol, GCP and the applicable regulatory requirements.

### Ethical and regulatory considerations

The Investigator will ensure that this trial is conducted in accordance with the principles of the Declaration of Helsinki and with relevant regulations, approved protocol and good clinical practice. Following Sponsor approval, the protocol, informed consent form, participant information sheet and proposed advertising material has been approved by the Oxford Tropical Research Ethics Committee (OXTREC) (reference number 28-20) and the Nepal Health Research Council (reference number 2291). The decision from the remaining review boards is pending.

The rights of the participant to refuse to participate in the trial without giving a reason must be respected. After the participant has entered into the trial, the clinician must remain free to give alternative treatment to that specified in the protocol, at any stage, if he/she feels it to be in the best interest of the participant. The reason for doing so, however, will be recorded; the participant will remain within the trial for the purpose of follow-up and for data analysis by the treatment option to which they have been allocated. Similarly, the participant must remain free to change their mind at any time about the protocol treatment and trial follow-up without giving a reason and without prejudicing his/her further treatment.

All participants will receive the best available treatment of typhoid fever, following local and national guidelines. They will benefit from the frequent and careful follow-up of their condition throughout the treatment of their typhoid fever and for up to 28 days from randomization.

The risks of participation are few. Azithromycin and cefixime are commonly prescribed drugs and there is widespread experience and expertise concerning their safe use. The choice dose, route of administration and duration of study treatment follows the international guidance for the treatment of typhoid fever. Previous trials have demonstrated the safety of this or similar regimens.

Against these minimal risks, trial participants may benefit from receiving these antibiotics for treatment of their suspected or confirmed typhoid fever. In addition, all participants will benefit from the careful observation and follow-up over 28 days from enrolment, which will allow complications of typhoid fever to be rapidly identified and managed.

The risks and benefits of participation will be communicated in two ways. First, all potential participants or their family members will be given a participant information sheet clearly listing the risks and benefits of the trial. Second, all potential participants (or their families) will be able to discuss participation with their consulting doctor who will be able to address questions not covered or arising from the participant information sheet.

Participants’ confidentiality will be maintained throughout the trial. Data submitted to Nepal CTU and samples sent to central testing facilities will be identified only by the trial number and participant initials.

The Principal Investigator shall submit once a year throughout the clinical trial, or on request, an annual progress report to the REC, HRA (where required), host organisation, funder (where required) and Sponsor. In addition, an End of Trial notification and final report will be submitted to the local and national ethics committee, host organisation and Sponsor within 12 months of completion of the study.

The study will comply with the General Data Protection Regulation (GDPR) and Data Protection Act 2018, which require data to be de-identified as soon as it is practical to do so. The processing of the personal data of participants will be minimised by making use of a unique participant study number only on all study documents and any electronic database(s), with the exception of the CRF, where participant initials may be added. All documents will be stored securely and only accessible by study staff and authorised personnel. The study staff will safeguard the privacy of participants’ personal data.

